**Fig. 1 Fig1:**
[figure not shown]
Trocar placement; blue = 5 mm assistant trocar, green = 11 mm assistant trocar, red = 8 mm da Vinci® trocars

**Fig. 2 Fig2:**
[figure not shown]
Intraoperative anatomy. **a** As seen from the cranial, intraperitoneal position of the camera. **b** After incision of the peritoneum along lateral umbilical fold. **c** After the PFs are created. **d** After fixation of the PFs. Asterisk indicates fixation to the pelvic floor using Vicryl 4/0 sutures; black star indicates vesicourethral anastomosis

The foley catheter can now be grabbed and moved ventrocranially. Now, the dorsal bladder neck is cut through. The anterior part of Denonvilliers’ fascia is severed, the spermatic duct and seminal vesicles identified, dissected, and held up/stretched. The anterior wall of the rectum can now be separated from the posterior part of the prostate either above or below the Denonvillier’s fascia depending on the nerve-sparing or non-nerve-sparing attempt. Depending on the preoperative agreement the neuro-vascular bundle is saved on both sides, one side or not saved in order to achieve higher oncologic safety. After apical separation, the urethra is incised and the foley catheter moved ventrally, which allows the separation of the posterior part of the urethrae. The prostate/specimen is placed in the ExBag® (Medtronic, Dublin, Ireland) specimen pouch. Bleeding is stopped using 4/0 Vicryl sutures and/or bipolar. After performing the dorsal Rocco stitch using a 3/0 V-loc™ barbed suture (Covidien, New Haven, USA), the vesicourethral anastomosis is sutured starting at 5 and 7 o’clock in lithotomy position and using a bidirectional 3/0 V-loc™ barbed suture (Covidien, New Haven, USA). Before the anastomosis is closed at 12 o’clock, a new foley catheter is inserted under visual control and the vesicourethral anastomosis is closed. Afterwards, the ventral Rocco stitch is performed. Next, the anastomosis is controlled for its integrity by filling the bladder with a minimum volume of 60 ml NaCl using the inserted catheter. Hereafter, the surgeon is informed about the result of patient randomization.

The ventral peritoneum is incised laterally on both sides to create the PF (Fig. 2c). Those PF are fixated to the pelvic floor opposite to the region of the lymphadenectomy using 2 interrupted 4/0 Vicryl (Ethicon Inc., Cincinnati, USA) sutures (Fig. 2d). Figure 3 shows intraoperative pictures of the creation and fixation of the peritoneal flap on the right side.

**Fig. 3 Fig3:**
[figure not shown]
Intraoperative anatomy, as seen from the cranial. **a** The dashed line on the peritoneum indicates, where the incision for the PF is to be made. **b** The flap has been created; the big white arrow indicates where the PF is flapped over to. **c** The flap after its fixation, the two little white arrows indicate, where the PF has been fixed to the pelvic floor

As the last step, the operating field and the trocars’ entry points are inspected for bleeding or damages and the specimen is removed after expanding the entry point of the camera trocar. No wound catheters are placed, since the standardized procedure in RALP at our department does not include drain placement. This approach is supported by the result of a recent meta-analysis published in August 2020, which found a reduction in postoperative complications after radical prostatectomy when drainage was omitted (odds ratio (OR)[95% confidence interval (CI)]: 0.62[0.44;0.87], *p* = 0.006), while there were no differences for re-intervention (OR [CI]: 0.72[0.39;1.33], *p* = 0.300), lymphocele OR [CI]: 0.60[0.22;1.60], *p* = 0.310), hematoma (OR [CI]: 0.68[0.18;2.53], *p* = 0.570), or urinary retention (OR [CI]: 0.57[0.26;1.29], *p* = 0.180) between drainage and non-drainage, concluding that “the omission of drains can be recommended for standardized RP (...) cases [32]”. A more recent study from September 2020 comes to the same conclusion and states “pelvic drainage may be omitted after RALP without increasing postoperative complications or prolonging the hospital stay [35].”

##### Group B: Control

All the surgical steps taken are identical to the intervention group with the exception that no flaps are created after suturing the vesicourethral anastomosis. The surgeon is informed about the result of patient randomization at the same point in time. Instead of creating PFs, the situs remains as it is at the end of the operation with the previously incised peritoneum laying loose in its original position. The surgical technique in the control arm reflects the standard procedure. Small variations according to the surgeon’s preference, such as the order of the right- and left-sided lymphadenectomy or using clips during lymphadenectomy and their amount, are allowed but must be recorded in the operation protocol. No drainages will be placed.

#### Adherence

Since the PELYCAN study is an interventional study with a 6-month follow-up as well as a sonographic examination at the day of hospital discharge, we do not expect adherence problems. The sonographic examinations for lymphoceles reflect the department’s standard of care and are performed on all patients, who receive RARP with LND - independently of study participation.

#### Concomitant care

To us, there is no known concomitant care or intervention, which could possibly affect the outcome in terms of a cointervention bias. All patients receive the same pre-, peri- and postoperative care according to local standard operating procedures.

A difference exists in postoperative anticoagulation therapy depending on pre-existing medical conditions. Some patients are in need of therapeutic anticoagulatory whereas all others will receive a low molecular weight heparin for thrombosis prophylaxis for 4 weeks postoperatively as standard of care according to current guideline recommendations. Hence, we will stratify for therapeutic or prophylactic anticoagulatory therapy.

### Outcomes

#### Primary endpoint

Difference between the two treatment arms in proportions of patients showing a symptomatic lymphocele within 6 months postoperatively. A symptomatic lymphocele is defined as sonographically detectable fluid accumulation in the area of the previously performed LND with the need of an interventional or operative therapy due to one of the following symptoms
Lower abdominal pain (after ruling out differential diagnosis)Deep vein thrombosis/leg swelling/lymph drainage problemsSuperinfection (fever/sepsis)

Data will be collected directly from the patients. These data will be complemented by the information gathered from the out-patient urologists, who treat the patients in an ambulant setting and perform their oncological follow-up.

#### Secondary outcome measures

For the secondary endpoint asymptomatic lymphocele at the time of discharge, ultrasonography will be performed by the assessors at the day of discharge. The assessors are blinded to the treatment group. Performing ultrasonography reflects the department’s standard of care. Asymptomatic lymphocele is defined as a sonographically detectable accumulation of fluid without symptoms. Furthermore, we will conduct a follow-up 6 months postoperatively. We will contact the patient directly. All patients gave informed written consent to be contacted. Lymphocele symptoms (pain, superinfection, deep vein thrombosis, or need for drainage insertion) will be assessed separately. Further secondary endpoints include:
Rates of asymptomatic lymphoceles at the time of dischargeThe combined endpoint of asymptomatic lymphoceles at the time of discharge and symptomatic lymphocelesQuality of Life (QLQ-C30, EORTC)Rehospitalization rate within 6 months after surgical treatmentRe-intervention rateLymphedema and/or erysipelasDeep vein thrombosisPerioperative parameters (operating time, complication (Clavien-Dindo & Comprehensive Complication Index, blood loss)Length of hospital stay

#### Participant timeline

During the PELYCAN trial (Fig. 4), every patient, who will receive RARP will be handed patient, who will receive RARP will be handed out the patient education and informed consent materials, when he registers for his appointment with our secretary and trained research nurses. All participants receive the same information sheet and consent form. It is highlighted that the agreement to participate is voluntary. The patient is given enough time to study the participant education. All members of the admission team (nurses and admitting doctors) have been trained in detail about the study and its content. The admitting doctors are specialists only. All patients will be seen and screened by the admission doctor at their pre-admission appointment at our outpatient clinic. Their current medication is assessed and the QLQ-C30 (EORTC) is completed by the patients. All patients, who decide about receiving the operation on their own, are determined to have sufficient decisional capacity regarding trial participation. Participants not being able to speak or read German and patients with previous history of head injury, dementia, or psychiatric disease and patients lacking the decisional capacity for the operation itself are considered to lack the decisional capacity for study participation. If eligible, patients are invited to participate in the trial and informed consent is obtained. The patients’ questions will be addressed carefully.

**Fig. 4 Fig4:**
[figure not shown]
PELYCAN-trial flow diagram according to SPIRIT [33]

Patients will receive ultrasonography examination at the day of discharge. The assessor will be the responsible ward doctor, who is blinded to group assignment. The main outcome interests are the occurrence of symptomatic lymphoceles. Patients will be assessed using questionnaires, which will be sent via email or post 6 months postoperatively. For data completion, we will also contact the patients’ outpatient urologists, who are responsible for the follow-up and medical/oncological aftercare. This increases the validity of our data. The questionnaires will be designed with questions which only can be answered dichotomously (“yes” or “no”). By that, we assure reproducible data. Additionally, patients will be sent the same quality of life (QoL) questionnaire they already have answered preoperatively (QLQ-C30, EORTC). Please refer to Table 1 for the detailed SPIRIT participant timeline.

**Table 1 Tab1:** Participant timeline (adapted from the original table)

Timepoint	Study period						
	Staff members	−t1	0	t1.1	t1.2	t2	t3
Activity/assessment		Screening and consent	Allocation	Surgery	Peritoneal flap	Day of discharge	6-month follow-up
**Enroll**							
Eligibility screening	SC	x					
Informed consent	AD	x					
Allocation	SC		x				
**INT**							
Group A (PELYCAN)	OS			x	x		
Group B (control)	OS			x			
**Assessments**							
Pre-existing medical conditions	AD	x					
Medication	AD	x				x	
Abdominal ultrasound	AD	x				x	
Quality of life (QLQ-C30, EORTC)	AD, PU	x					x
Lymphocele (symptomatic/asymptomatic)	WD, PU					x	x
Lymphocele symptoms	WD, PU					x	x
Lymphedema/erysipelas	PU						x
Rehospitalization	PU						x

*Enroll* enrolment, *INT* intervention, *SC* study coordinator, *AD* admission doctor, *OS* operating surgeon, *WD* ward doctor, *PU* private urologist

#### Sample size

The sample size was calculated on the basis of the primary hypothesis. The incidence of symptomatic lymphoceles after RARP has been listed with 2–15% [6], 0–8% [17], and 9–51% [31, 36]. The incidence of post-prostatectomy *lymphoceles in general* has been described with an occurrence of 10–18%, [1], 30% [17], and up to 61% [37]. The previously conducted studies on PF for lymphocele prevention list the incidences for *symptomatic lymphoceles* in their control groups with 4.6% [16], 11.6 [6], 4.1% [17], 9,1% [20], and 9.7% [20], respectively. Stolzenburg et al. have been describing 8.3% *asymptomatic lymphoceles* in their matched-pair cohort; Bründl et al. described an incidence of asymptomatic lymphocele in 24.2% in the control group within the first 90 days postoperatively [16, 20].

Therefore, we assume a rate of symptomatic lymphoceles of 10% for the control group which can be reduced to 2% for the PELYCAN group. Using a power of 80% and a one-sided α (type 1 error) level of 0.025, we calculated a sample size of *n* = 141 per arm, in total *n* = 282. Assuming a drop-out rate of approximately 6%, we aim for a study population of 300 patients. However, due to uncertainty in the actual incidence of symptomatic lymphoceles and the effect of the intervention, sample size recalculation will be performed after an interim analysis in an adaptive study design after completion of the follow-up of the first 120 patients. According to the results of the sample size recalculation, the trial might be terminated for futility or efficacy by the PI or the sample size will be adapted [38, 39]. The maximum number of patients will be 1000.

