**Methods/design:**

PELYCAN is a parallel-group, patient- and assessor-blinded, phase III, adaptive randomized controlled superiority trial. Men with histologically confirmed prostate cancer who undergo transperitoneal RARP with pelvic LND will be randomly assigned in a 1:1 ratio to two groups—either with creating a peritoneal flap (PELYCAN) or without creating a peritoneal flap (control). Sample size calculation yielded a sample size of 300 with a planned interim analysis after 120 patients, which will be performed by an independent statistician. This provides a possibility for early stopping or sample size recalculation.

Patients will be stratified for contributing factors for the development of postoperative lymphoceles. The primary outcome measure will be the rate of symptomatic lymphoceles in both groups within 6 months postoperatively. Patients and assessors will be blinded for the intervention until the end of the follow-up period of 6 months. The surgeon will be informed about the randomization result after performance of vesicourethral anastomosis. Secondary outcome measures include asymptomatic lymphoceles at the time of discharge and within 6 months of follow-up, postoperative complications, mortality, re-admission rate, and quality of life assessed by the EORTC QLQ-C30 questionnaire.

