#### Blinding and blinding mechanism

To reduce performance bias, patients and assessors will be blinded to group allocation until 6 months after surgery [40]. Randomization will take place 1 day before surgery. The operating surgeon will be informed about group allocation after the vesicourethral anastomosis is finished. This late point of involving the surgeon guarantees a consistent procedure and thereby minimizes the surgeon’s bias.

By using a unique randomization ID for each patient, patients, outcome-assessors for in-patient treatment and examination of lymphoceles as well as the care providers/outcome-assessors for examination and follow-up after discharge will be blinded. Data collectors will be kept blinded as well until the data collection will be finished.

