##### Emergency unblinding

To maintain the overall quality and legitimacy of the clinical trial, code breaks should occur only in exceptional circumstances when knowledge of the actual treatment is absolutely essential for further management of the patient. If unblinding is deemed to be necessary, the investigator should use the system for emergency unblinding through contacting the PI or the people responsible for study coordination. The investigator is encouraged to maintain blind as long as possible. The actual allocation must not be disclosed to the patient and/or other study personnel including other site personnel nor should there be any written or verbal disclosure of the code in any of the corresponding patient documents. The Investigator must report all code breaks (with reason) as they occur.

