### Data monitoring

#### Formal committee

No data monitoring committee will be installed. However, in order to ensure patient safety, all perioperative complications will be assessed and analyzed.

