#### Auditing

There will not be any auditing. Since there is no sponsor and the investigators do not have a financial nor a non-financial incentive neither, the study will be performed independently.

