### Access to data

The principal investigator will be given access to the full data sets. To ensure confidentiality, data dispersed to all other investigators and project team members will be blinded of any identifying participant information.

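### The PI is named as the person who may stop the trial after the interim analysis, and nothing in the protocol keeps the comparative result from the PI while most patients lie beyond the interim cohort

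*Protocol article*

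**What the plan says.** - **Interim analysis.** The abstract (Methods/design) announces a "planned interim analysis after 120 patients, which will be performed by an independent statistician". Under Sample size, it takes place once those 120 patients have completed follow-up.
- **Decision.** The same section says that, depending on the recalculation, "the trial might be terminated for futility or efficacy by the PI or the sample size will be adapted". It cites two references and sets a maximum of 1000 patients. The PI is named for termination; nobody is named for setting the new sample size.
- **Oversight.** Formal committee: "No data monitoring committee will be installed". Auditing: "There will not be any auditing".
- **Access.** Access to data: "The principal investigator will be given access to the full data sets". No time limit is given and allocation is not excluded. The restriction on other team members concerns identifying information.
- **Blinding.** Blinding and blinding mechanism covers patients, outcome assessors and care providers, and adds: "Data collectors will be kept blinded as well until the data collection will be finished". The PI is not on the list.
- **Error control.** Statistical methods (Outcomes) says the primary p-value will be adjusted for the adaptive design.

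**The concern.** An interim comparison is safe for the rest of a trial when the people who run it do not learn the result. Here the text gives the stopping decision to the PI and puts no barrier between the PI and the comparative data.

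Someone who knows how the arms compare can, without intending to, change how keenly patients are recruited, how the remaining operations are done, or how actively outcomes are pursued. The trial is exposed to this in three ways. It starts at a single centre (Study setting). The primary endpoint requires that a lymphocele was judged to need interventional or operative therapy (Primary endpoint), so it contains a clinical decision. The endpoint is collected by contacting patients and their urologists (Data collection, Primary outcome). An adjusted p-value cannot remove a bias that enters through conduct.

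**Working it through.** **1. The plan's own sample size.** Inputs from Sample size: 10% versus 2%, one-sided α = 0.025, power 80%. With pooled variance under the null, n per arm = [1.96·√(2·0.06·0.94) + 0.8416·√(0.10·0.90 + 0.02·0.98)]² / 0.08² = (0.658 + 0.279)² / 0.0064 ≈ 137.2, so 138. The stated 141 is within 3% of this and has 81.1% power. 282 / 0.94 = 300 also agrees. The planned size is not in question.

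**2. Who decides, who sees the data, who is blinded.**

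| Question | Answer in the protocol |
|---|---|
| Who computes the interim analysis? | Independent statistician (abstract) |
| Who may stop for efficacy or futility? | The PI (Sample size) |
| Who sets the new N? | Not stated |
| In what form is the result passed on? | Not stated |
| Committee between statistician and PI? | None (Formal committee) |
| Is the PI's access limited by time or arm? | No limit stated (Access to data) |
| Is the PI listed as blinded? | No (Blinding and blinding mechanism) |

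The assignment of the decision is stated text. An analysis plan could add boundaries, but it would have to contradict the Sample size section to move the decision away from the PI.

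**3. Share of the trial exposed.**
- Planned size: (300 − 120)/300 = 180/300 = 60%.
- Maximum size: (1000 − 120)/1000 = 880/1000 = 88%.

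Not all of these patients would be recruited after the result. Trial status reports 140 randomized by 16 August 2020, so at least 20 patients beyond the first 120 were already in the trial by then. For patients still within their 6 months, only follow-up could be affected.

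**4. What a look at 60 per arm can show.** Assuming an even split of the 120 patients, the expected events are 60 × 0.10 = 6 and 60 × 0.02 = 1.2, in total 7.2. From exact binomial distributions:
- Under 10% versus 2%, P(no flap event) = 0.98^60 = 0.298.
- Under 10% versus 2%, P(control exceeds flap by 2 events or fewer) = 0.184.
- With no effect, P(flap leads by 4 or more) = 0.087 at 6% in both arms and 0.142 at 10%.

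So the comparison is noisy and easy to misread in either direction. These figures do not measure the bias itself, which cannot be computed from the document.

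**5. What the announced N can reveal.** The protocol fixes no recalculation formula. As an illustration, assume the formula in step 1 is applied to the observed rates at 60 per arm:

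| Events, control vs flap | Recalculated total N |
|---|---|
| 6 vs 1 | 246 |
| 6 vs 2 | 438 |
| 6 vs 3 | 870 |
| 6 vs 4 | 2158 (above the maximum of 1000) |

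Under such a rule an exact N comes close to disclosing the interim effect, even if no arm-level figure is passed on. Coarse preset steps reduce this.

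**The case against.** The case against is substantial, and parts of it stand.

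- **The PI receives the unblinded result.** A reader might infer this, but no section says so. A bare recommendation from the statistician would be compatible with the text. What stands is that nothing requires that form.
- **The PI chooses the sample size.** A reader might infer this too. The sentence attaches the PI to termination only.
- **The decision has no rule behind it.** The text ties the decision to the recalculation and cites adaptive-design references. Boundaries and formulas may sit in the full protocol or analysis plan, and their absence from an article is no defect.
- **The type I error is inflated.** This would need unadjusted looks, and Statistical methods promises an adjusted primary p-value.
- **The PI's other roles.** Amendments also need ethics committee approval (Protocol amendments). Access to data is mainly about identifiers. Code breaks through the "system for emergency unblinding through contacting the PI or the people responsible for study coordination" concern individual exceptional cases and are not a route to an interim comparison.
- **Existing safeguards.** Patients, assessors and data collectors are blinded. Randomization is run by an uninvolved person, and the surgeon learns the arm only after the anastomosis, so the node dissection is done blind. Following up one arm harder than the other would need individual allocations, not just a summary. These safeguards narrow the ways in which bias can enter. They do not cover the PI, and blinding of patients and assessors is stated only until 6 months after surgery, the point the first 120 have reached at the interim analysis.

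**Conclusion.** The point holds as a gap in who may decide and who may see the comparison: the PI is the named stopping authority, there is no committee, no limit on arm-level access is stated, and the PI is not among those kept blinded. The exposed share is 60% of patients at the planned size and up to 88% at the maximum, less those already operated on when the result becomes available. The direction and size of any bias are unknown.

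The conclusion rests on the article as published. If the full protocol or analysis plan already routes the interim result around the PI, the published wording is wrong and needs correcting, but the conduct is sound. Neither an actual disclosure to the PI nor a failure of type I error control is shown. The change should be made, because it is cheap and bias of this kind cannot be repaired in the analysis.

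**What to change.** 1. **Sample size.** Replace termination by the PI with the following: the independent statistician applies the pre-specified adaptive-design rule, signed and dated before any unblinded look, and returns only *stop* or *continue to N*, with N taken from preset steps up to 1000.
2. **Access to data.** State that the PI has access to arm-level data only after database lock. Align Data Availability with this.
3. **Blinding and blinding mechanism.** Add the PI to those kept from comparative results until then.

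**Timing.** 119 patients had agreed to take part six months after recruitment began (Recruitment), the first randomization was on 2 September 2019, and 140 had been randomized by 16 August 2020 (Trial status). Six-month data on the first 120 were therefore complete at some point between about September 2020 and mid-February 2021. This protocol version is dated 17 October 2020, so the rule is needed at once. If the look has already taken place, the report should state what was passed to the PI and when.

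**Cost.** Protocol wording and a short signed rule. The statistician is already planned and no committee is required. The PI gives up discretion over stopping, and the recalculated N is slightly coarser than an exact formula would give.
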